### Sample size calculation

2.5

We calculate the sample size with the following formula for the rate comparison of two groups (Sakpal, 2010):$$n=\frac{\lambda }{2{\left(\arcsin\sqrt{P_{\max}}‐\arcsin\sqrt{P_{\min}}\right)}^{2}}$$We assume α = 0.05, β = 0.2 and ν = 3–1 = 2, then λ = 8.84, and we set *P*
_max_ and *P*
_min_ as the maximum and minimum fluctuation rates of during sputum suction in our pre‐trials (54.6% and 20.9%, respectively), then we come to the result of *n* ≈ 78. Furthermore, considering that the attrition rate of about 10% of the study participants, the number of patients included in each group should be at least 86. Therefore, a total of 172 patients are intended to be included.

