### Outcome assessment

2.9

The outcomes collected and analysed in this present study are as follows: (a) the ICP (mmHg) level before suctioning, at the end of suctioning, and at 5 and 10 min after suctioning; (b) the pulse oxygen saturation (SpO_2_,%) and heart rate (times/min) before suctioning, at the end of suctioning, and at 5 and 10 min after suctioning; (c) the estimated sputum volume (ml) for each suction; (d) the incidence of ventilator‐associated pneumonia(VAP): the diagnosis and treatment of VAP will be in comply with related guidelines (Ardehali et al., 2020; Liapikou et al., 2019; Shi et al., 2019); (e) the duration of mechanical ventilation (days); and (6) the length of ICU stay (days).

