### Statistical analysis

2.10

SPSS 23.0 software will be used for data analysis in the present study. The enumeration data will be expressed with mean ± standard deviation (*SD*), and the categorical variable data will be expressed with percentages (%). Test for normality will determine whether to use parametric test (independent *t* test/paired *t* test) or (Mann–Whitney test/ Wilcoxon's test). In this present study, *p* < .05 will be considered statistically significant.

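### No outcome or ICP time point is designated primary, the sample size rests on an unlisted quantity, and one unadjusted 5% threshold covers about 13 implied between-arm comparisons

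*Protocol article*

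**What the plan says.** Section 2.9 (Outcome assessment) opens with "The outcomes collected and analysed in this present study are as follows" and gives six lettered or numbered items covering seven outcomes. The first is "the ICP (mmHg) level before suctioning, at the end of suctioning, and at 5 and 10 min after suctioning". SpO2 and heart rate follow on the same four-point schedule. Then come "the estimated sputum volume (ml) for each suction", VAP incidence, days of mechanical ventilation and days in ICU. None is called primary or secondary, and the abstract repeats the list on equal terms.

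Section 2.5 (Sample size calculation) compares two rates, 54.6% and 20.9%, described "as the maximum and minimum fluctuation rates of during sputum suction". It does not say what fluctuates or by how much, and no such rate is in the outcome list.

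Section 2.10 (Statistical analysis) names independent and paired t tests with their rank-based counterparts. It names no repeated-measures model and closes with "In this present study, *p* < .05 will be considered statistically significant".

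The title and the Discussion put ICP in front. Section 3 (Results) expects closed suction to keep ICP steadier and expects the arms to be equal on sputum volume and VAP. Sections 2.1 and 2.7 say that outcome assessment is not blinded.

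**The concern.** A 5% significance level has its usual meaning only when it is tied to a test chosen in advance. Here several outcomes, three of them measured repeatedly, share one threshold, and nothing says which result decides the trial. Even a reader who takes ICP as the obvious target cannot tell whether the end-of-suction, 5-minute or 10-minute reading counts, or a change score or summary of them.

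The sample size does not settle this, because it is built on a proportion that is not a listed outcome. So neither the stated alpha nor the stated power belongs to any outcome that will be reported.

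Section 2.8 has suction performed as the child needs it, so one child may contribute many episodes. Which episode, or what per-child summary, enters the comparison is also open. With unblinded assessors and a stated expectation in favour of closed suction, prespecification is the main protection against selecting a favourable result after the fact.

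**Working it through.** **The plan's own figures.** The article states no family-wise error rate, so there is none to reproduce. The nearest stated figure is n ≈ 78 per group in section 2.5. The printed formula with the printed inputs gives an arcsine difference of 0.3567 and n = 8.84 / (2 × 0.3567²) = 34.7, not 78. That mismatch is a separate matter and does not enter the calculation below.

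**Step 1: count the comparisons.** From section 2.9:
- ICP, SpO2 and heart rate, each at three post-suction times: 3 × 3 = 9
- sputum volume, VAP, ventilation days, ICU days: 4
- total: 9 + 4 = 13

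One test per time point is an inference from section 2.10, which names only two-sample and paired tests. If pre-suction values were also compared, the count would be 3 × 4 + 4 = 16.

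**Step 2: independent tests.** With no true difference on any outcome, the chance of at least one p < .05 among k independent tests is 1 − 0.95^k.
- k = 13: 1 − 0.95^13 = 48.7%
- k = 16: 1 − 0.95^16 = 56.0%
- k = 3 (ICP only): 1 − 0.95^3 = 14.3%
- k = 1 (one designated primary): 5.0%

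**Step 3: correlated tests.** The documents give no correlations, so these are assumptions. Thirteen two-sided z tests at 0.05 were simulated with 400,000 replicates and all null hypotheses true. One common correlation was used among the three times of an outcome and another across outcomes.

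| Within outcome | Across outcomes | At least one false positive |
|---|---|---|
| 0.5 | 0 | 45.4% |
| 0.8 | 0 | 40.2% |
| 0.9 | 0 | 37.3% |
| 0.8 | 0.3 | 36.0% |
| 0.8 | 0.5 | 30.4% |
| 0.95 | 0.5 | 26.8% |

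With both correlations at zero the simulation gave 48.6%, in agreement with the exact 48.7%.

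**Step 4: a limiting case.** If the three times of each repeated outcome were perfectly correlated, they would act as one test, leaving 3 + 4 = 7. If those seven were independent, the figure would be 1 − 0.95^7 = 30.2%. For ICP alone, perfect correlation brings 14.3% down to 5%, so the ICP-only figure lies between 5% and 14.3% for correlations between one and zero.

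**Step 5: scale of a correction.** A Bonferroni threshold over 13 tests would be 0.05 / 13 = 0.0038.

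**The case against.** The strongest reply is that ICP is plainly the target. It is in the title, comes first in the outcome list, is the focus of the Discussion, and is the only outcome on which section 3 expects closed suction to do better. On that view the relevant family is the three ICP times, with inflation of at most about 14%. Much of this stands: section 3 makes it less likely that a superiority claim would be drawn from any of the 13 comparisons. It does not remove the point, because ICP is never designated and none of its three times or any summary is chosen.

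A second reply is that an analysis plan may exist and an article condenses. That is fair for the multiplicity procedure itself, such as Holm or a fixed order. It is not fair for the choice of primary outcome, which is a protocol decision and one on which the sample size should depend. The article has full sections on outcomes, sample size and analysis, and together they fix an unranked list with a blanket threshold.

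Two stronger readings are tempting. A reader might infer that the false-positive chance is at least 40%. It is not shown to be: 40% needs a within-outcome correlation of about 0.8 and none across outcomes. The latter is hard to defend when ventilation days and ICU days are likely to move together and ICP, SpO2 and heart rate are read in the same child at the same moments. A reader might also add the paired tests within arms, up to 3 × 3 × 2 = 18 more. Section 2.10 names paired tests but does not say where they apply, and they play no part in the figures above.

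**Conclusion.** The point holds. No outcome and no ICP time is primary, the sample size refers to a quantity outside the outcome list, and one unadjusted threshold applies throughout. If every post-suction time is tested separately and the arms truly differ on nothing, the chance of at least one false positive is about 49% under independence. It is roughly 27–45% for assumed correlations of 0.5–0.95 within outcomes and 0–0.5 across them. For ICP alone it is up to about 14%. Even the lowest of the 13-test figures, 26.8%, is more than five times the nominal 5%.

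The count of 13 is inferred from the tests named. The plan sets a threshold; it does not say that each comparison will be presented as a finding. The registry record is not at hand, so nothing can be said about whether a primary outcome is named there. This should be corrected, but it does not invalidate the design.

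**What to change.** Before any between-arm analysis, amend sections 2.9 and 2.10 as follows:
- Name one primary outcome. One candidate is the between-arm difference in ICP at the end of suctioning, adjusted for pre-suction ICP and tested at two-sided 0.05. The documents do not dictate this time over 5 or 10 min; what matters is that one is fixed and justified.
- State the per-child rule for repeated suction episodes, for example a specified episode or a specified summary across episodes. Without it, the choice of result stays open even with a named time point.
- Test the remaining ICP times in a fixed order, each only if the preceding test is significant.
- Report all other outcomes as secondary with 95% confidence intervals and no confirmatory claim, or with Holm adjustment.
- In section 2.5, give the sample-size basis for the chosen primary, or say openly that the existing calculation refers to a different endpoint.

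The cost is mainly wording, plus aligning the registration if it differs, and no new measurements are needed. Whether 172 children suffice for a continuous ICP primary cannot be judged here, because the article gives neither a standard deviation nor a target difference in mmHg. The downside is that secondary results can no longer be claimed on p < .05 alone.

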## RESULTS

3

Our study is planned to commence on 1 September 2020 and is expected to run until 31 August 2022, with a total duration of 24 months. We will use the intention‐to‐treat analysis to retain the randomized information as much as possible, and we will compare and adjust the characteristics to minimize the homogeneity of participants. We have conducted a pilot study with four patients to check the feasibility of the study, and it is feasible in our department. And based on the results of pilot study, we expected that the closed suctions may have more advantages in stabilizing the ICP level, and it may have the equal effects in the suctioned sputum volume and preventing the VAP. The results are expected to be shared in August 2022.

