### Trial status

2.3

This present RCT has been registered in China Clinical Trial Registry (http://www.chictr.org.cn, ChiCTR2000030963). We have registered it on 20 March 2020. We are intended to recruit the participants on 1 September 2020, and recruitment will be completed approximately on 31 August 2022.

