### Participants

2.4

The children with severe brain injury admitted to the surgical ICU (SICU) in our hospital from 1 September 2020 to 31 August 2022 will be considered for inclusion.

The inclusion criteria are as follows: (a) the age of children should be >28 days and <18 years; (b) the diagnosis of severe brain injury should comply with the relevant guidelines (Carney et al., 2017; Gao, 2017); (c) the children will undergo mechanical ventilation, and all the participants will be under the 24‐hr cerebral protection; (d) the children do not have other severe organ dysfunction, such as congenital heart disease; and (e) the guardian or relatives will be informed and agree to participate in this present study.

The exclusion criteria are as follows: (a) children with pneumothorax, atelectasis or other serious congenital diseases or respiratory infections; and (b) children or the guardians will not consent to participate in this present study and sign the informed consent.

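### The study end and the results date both fall within the recruitment period, leaving no time to complete ventilation days, ICU days and VAP for the last children enrolled

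*Protocol article*

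**What the plan says.** All of these statements are in the protocol article.

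- **Trial status (2.3), start:** "We are intended to recruit the participants on 1 September 2020".
- **Trial status (2.3), end of recruitment:** "recruitment will be completed approximately on 31 August 2022".
- **Participants (2.4), admission window:** children admitted "in our hospital from 1 September 2020 to 31 August 2022 will be considered for inclusion". The abstract gives the same window.
- **Results (3), study duration:** the study "is expected to run until 31 August 2022, with a total duration of 24 months".
- **Results (3), reporting:** "The results are expected to be shared in August 2022". The same section commits to an intention-to-treat analysis.
- **Outcome assessment (2.9):** VAP incidence is item (d), and the list closes with "e) the duration of mechanical ventilation (days); and (6) the length of ICU stay (days". ICP, SpO2 and heart rate are recorded up to 10 minutes after a suction, and sputum volume is recorded for each suction.
- **Sample size calculation (2.5):** "a total of 172 patients are intended to be included", which is 78 per group raised to 86 for about 10% attrition.
- **Statistical analysis (2.10):** t tests, or Mann-Whitney and Wilcoxon tests if normality fails.

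**The concern.** The recruitment window and the total study duration are the same 24 months, and reporting falls in the last of them. A child admitted in late August 2022 is eligible, but on these dates cannot contribute a finished ventilation episode or ICU stay, and VAP can still develop after the stated study end.

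Three of the six outcome groups are exposed: VAP, ventilation days and ICU days. If the dates were followed, the analyst would have two choices. One is to leave out randomised children whose stay is unfinished. The other is to enter the days accrued so far as if they were the final value. The tests in section 2.10 treat every duration as complete and have no means of handling a stay that is still running. Children still in the ICU at any calendar cut tend to be the long stayers, so either choice pulls the reported durations down and misses late VAP.

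**Working it through.** **1. The plan's own figure.** From 1 September 2020 to 31 August 2022 inclusive is 730 days, or 24 months. The stated duration reproduces exactly. It also equals the recruitment window:

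follow-up after the last eligible admission = 730 − 730 = 0 days.

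**2. Accrual rate.** Inputs: 172 children (section 2.5) over 730 days, assumed uniform.

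172 / 730 = 0.2356 per day, and 172 / 24 = 7.17 per month.

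**3. Children still in the ICU on 31 August 2022.** The article gives no ICU stay, so a mean stay L of 7 to 28 days is assumed, counted from enrolment.

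expected number = 0.2356 × L; share of 172 = L / 730.

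| Assumed stay (days) | Children still in ICU | Share of 172 |
|---|---|---|
| 7 | 1.6 | 1.0% |
| 14 | 3.3 | 1.9% |
| 21 | 4.9 | 2.9% |
| 28 | 6.6 | 3.8% |

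This counts unfinished ICU stays. If ventilation takes place within the ICU stay, it cannot last longer, so the count is an upper limit for ventilation days and, largely, for VAP.

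**4. Data locked on 1 August 2022 so that results can appear that month.**

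not yet enrolled = 0.2356 × 31 = 7.3 children (31 / 730 = 4.2%).

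Adding those still in the ICU at that lock: 0.2356 × (31 + 7) = 9.0 children (5.2%) to 0.2356 × (31 + 28) = 13.9 children (8.1%). The two parts differ in kind. The 7.3 are not yet randomised; only the other 1.6 to 6.6 are randomised children with incomplete data.

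**5. Effect on the mean ICU stay if unfinished stays were entered as final on 31 August.** If every stay lasted exactly L days, a child still in the ICU would on average have half the stay left:

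shortfall = (L / 730) × (L / 2) days.

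For L = 7 this is 0.03 days (0.5% of 7). For L = 28 it is 0.54 days (1.9% of 28). Stays that vary around the same mean would give a larger shortfall.

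**6. Outcomes not touched.** ICP, SpO2, heart rate and sputum volume are complete within 10 minutes of each suction. For a child already treated, no calendar cut removes values already recorded.

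**The case against.** The strongest reply is that the dates are soft. The article calls them approximate, planned or expected, and it sets no data cut-off, censors no stay and drops no late entrant. The 24 months may only restate the recruitment window. The definition of study end and database lock commonly sit in a full protocol or analysis plan that is not shown. This stands in part: truncation follows from the dates and is not a stated rule, and the absence of a lock procedure is not itself a fault. It does not remove the conflict, because the study end and the results date are both stated, and they clash with the admission window.

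A reader might infer three stronger things that the document does not support.

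- **That the comparison of open with closed suctioning would be biased.** A common calendar cut falls on both randomised groups. It lowers the level of the durations in each, and nothing in the document shows that it shifts the difference between them.
- **That a lock a month early would breach intention-to-treat.** The 7 or so children lost that way would not yet be randomised. The result is a smaller sample, and 7 is fewer than the 16 children (2 × (86 − 78)) added for attrition. Intention-to-treat is at stake only for randomised children whose unfinished stays are left out.
- **That early results would distort the remaining enrolment.** Nurses and outcome observers are unblinded (sections 2.1 and 2.7), but August includes its last day. The overlap is at most a month and may be nil, and no effect can be sized from the document.

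**Conclusion.** The point holds as an internal contradiction in the timeline, and it is minor. The admission window, the study end and the results date cannot all be met with complete data on VAP, ventilation days and ICU days.

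Taken literally, about 2 to 7 of 172 children (1.0% to 3.8%) would have incomplete values for these outcomes at 31 August 2022. Reporting from a 1 August lock would also leave out about 7 children not yet enrolled. These counts rest on uniform accrual and on an ICU stay of 7 to 28 days, which is an assumption.

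The consequence is some understatement of absolute durations and VAP incidence in both arms. Neither a biased treatment contrast nor any damage to ICP, the outcome named in the trial's title, has been shown.

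**What to change.** Keep 31 August 2022 as the last admission date. Define the end of data collection as ICU discharge or death of the last randomised child, or as a fixed number of days after the last randomisation. If a fixed number of days is chosen, say how a stay still running on that day is analysed. Lock the database and release results only after that point. In the Results section, correct the total of 24 months and the August 2022 reporting date to match.

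The cost is a few reworded sentences and results a few weeks to months later. No extra patients or staff are needed.

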## DISCUSSION

4

Mechanical ventilation plays a key role in life support for children with severe head injury, and the airway management during mechanical ventilation is essential to the prognosis of patients (Fraga Gomes Martins et al., 2019). Intratracheal sputum suction is an important part in the management of children with mechanical ventilation, which acts to keep the children's airway open by removing the sputum or secretions in the airway (Coppadoro et al., 2019). If the suction cannot remove the sputum of patients in a timely and effective manner, it will not only affect the oxygenation function of children, but also colonize a large number of sputum and bacteria in the lungs and increase the risk of VAP (Dexter & Scott, 2019; Rouze et al., 2018). However, it has been reported (Fraga Gomes Martins et al., 2019) that the suction during the mechanical ventilation may also lead to secondary brain injury. Therefore, how to ensure the effectiveness and safety of sputum suction is on the top research agenda of respiratory managements in children with mechanical ventilation.

Open suction and closed suction are the two of most commonly seen approaches of suction clinically. Hao et al. (Hao & Wang, 2018) have conducted a meta‐analysis on the effectiveness and safety of closed suction and open suction in adults, and a total of 9 RCTs have been included, and the results have shown that compared with open endotracheal suction, the closed endotracheal suction can prevent the occurrence of VAP and reduce the duration of mechanical ventilation, but it cannot reduce the mortality. It is worth noting that the quality of RCTs included in this study is limited, thereby the results obtained have limited insights into clinical setting. Meanwhile, the previous study (Lu et al., 2018) has shown that the frequency of changing the closed suction device has a significant effect on the colonization of bacteria at the tip of the suction tube. At present, there are still controversies (Shamali et al., 2019; Williams et al., 2018) about the advantages and disadvantages of closed and open endotracheal suction in the incidence of VAP, mortality and length of hospital stay. Therefore, there are still many controversies over the role of open and closed endotracheal suction in clinical practice, and further researches are needed.

ICP monitoring plays an important role in the treatment and prognosis of patients with brain injury. Several previous studies (Argent, 2019; Chen et al., 2019; Miles et al., 2020) have shown that there is a significant correlation between the changes in ICP and cerebral blood flow perfusion with various treatment and nursing procedures. The nursing operation of suction can lead to transient increase in ICP, but its long‐term effects remain unclear. Giancarlo et al (Galbiati & Paola, 2015) have systematically analysed 14 related studies and have pointed out that although the risk of ICP increasing above 20mm Hg during open suction is higher, it is still unclear which suction approach is more conducive to the maintenance of ICP and brain blood perfusion balance. Therefore, further research is needed to determine the best suction technique for nursing practice.

Several limitations must be considered in this present study. Firstly, even though we have organized a research team to collect the data, we cannot ensure all the normal nursing staff will follow the procedures as we designated, we cannot ensure data are collected on every suction episode, especially for those patient requires emergency suctioning, and the data may not be collected timely. We will conduct several trainings on the details of our procedure to ensure the accuracy of collected data. Secondly, sample size is not large in this present study, and there may be some differences in the suction pressure among different populations, and future studies with larger sample size and multi‐centre are needed.

To the best of our knowledge, there are very few studies focused on the role of open and closed endotracheal suctions and potential effects on the ICP in the children population. In this present study, we have aimed to assess the potential effects of open and closed endotracheal suction on ICP in the population of children, to provide credible evidence to the nursing care of airway. The results of this study are expected to provide basis for the suction practice of airway management in children.

